### Model fairness

Model performance will be evaluated within patient subgroups defined by demographic characteristics, social vulnerability factors, and specific comorbidities. Variables across which model performance will be compared include patient age, sex, race, ethnicity, and cancer status. In addition to standard measures of discrimination, false-negative rates will also be compared across patient categories [16].

### Missing data

Our primary analysis will use fixed-value imputation for continuous variables, for which missing values are replaced by the median value calculated among patients with observed data. For categorical variables, “missing/unknown” will be included as a separate category. We use these approaches for several reasons. First, due to potentially informative presence (i.e., a laboratory measurement is more likely to be ordered for patients for whom an abnormal value is suspected), data will not be missing at random [17]. Second, while multiple imputation (MI) may provide more accurate imputation in retrospective data [18], when used prospectively, it would likely require additional models to be implemented in real time for prediction of missing values. A sensitivity analysis will be performed comparing performance of models using MI and median-value imputation. A detailed simulation study comparing imputation approaches for real-time prediction will be reported separately.

### Statistical analysis

Patient encounter data will be summarized using median and interquartile range (IQR) for continuous variables and counts with percent for categorical variables. Encounter data will be summarized by cohort (derivation, temporal external validation, geographic external validation, and domain external validation) and by HA-VTE status. The rate of HA-VTE will be examined over continuous time and compared between cohorts. Statistical comparisons will be performed using chi-square tests for categorical variables and Kruskal–Wallis tests for continuous variables. A two-sided *p* value < 0.05 will indicate statistical significance. No adjustments will be made for multiple comparisons.

Model development will be performed within the derivation cohort described above. Data from validation cohorts will be kept fully external. Least absolute shrinkage and selection operator (LASSO) regression with tenfold cross-validation will be used for initial variable selection [19]. This will select the subgroup of variables minimizing cross-validation error. We will use the *C* statistic as the error measure to be optimized in the cross-validation process. LASSO variable selection will be performed using the “glmnet” package in R [20]. Restricted cubic splines will be considered for continuous variables. Variables selected in the LASSO procedure will be used in an unpenalized multivariable logistic regression model. Physician feedback regarding model complexity and variables necessary for inclusion will also be incorporated into the identification of the final prognostic model.

Performance of the unpenalized logistic regression model, fit using variables selected in the cross-validation procedure, as well as any additional variables identified by clinicians as necessary for clinical validity, will be reported in the derivation cohort as well as the temporal, domain, and geographic external validation cohorts. More complex models, such as random forest or XGBoost, will not be considered as there was minimal to no improvement in performance when using these models compared to logistic regression (data not shown). Predicted probabilities for each patient will be generated using the fitted logistic regression model object and the *predict()* function in R. Prediction performance will be quantified using measures of discrimination (*C* statistic [21]), calibration (calibration intercept, calibration slope, Brier score, integrated calibration index, and visual examination of non-parametric calibration curve), and distribution of predicted risk [22–24]. Model variable importance and odds ratios with 95% CI will be reported. Additionally, we will report model performance within pre-specified subgroups. Predictions in the external cohorts will be generated using the non-recalibrated model. Models with recalibrated coefficients may be considered if there is a substantial decrement in prediction performance. In such cases, recalibrated and non-recalibrated model performance will be reported and compared. We will follow TRIPOD + AI guidelines [11] for model reporting. All analyses will be conducted using the current version of R statistical software [25].

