**Methods:**

A retrospective cohort of 132,561 inpatient encounters (89,586 individual patients) at a large academic medical center will be collected, along with clinical and demographic data available as part of routine care. Data for temporal, geographic, and domain external validation cohorts will also be collected. Logistic regression will be used to predict occurrence of HA-VTE during an inpatient encounter. Variables considered for model inclusion will be based on prior demonstrated association with HA-VTE and their availability in both retrospective EHR data and routine clinical care. Least absolute shrinkage and selection operator (LASSO) with tenfold cross-validation will be used for initial variable selection. Variables selected by the LASSO procedure, along with those deemed necessary by clinicians, will be used in an unpenalized multivariable logistic regression model. Discrimination and calibration will be reported for the derivation and validation cohorts. Discrimination will be measured using Harrell’s *C* statistic. Calibration will be measured using calibration intercept, calibration slope, Brier score, integrated calibration index, and visual examination of non-linear calibration curve. Model reporting will adhere to the Transparent Reporting of a multivariable prediction model for Individual Prognosis Or Diagnosis guidelines for clinical prediction models using machine learning methods (TRIPOD + AI).

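### The LASSO penalty is tuned on the penalized fits, but the model used is an unpenalized refit that is never cross-validated; the mismatch is certain, its size conditional

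*Protocol article*

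**What the plan says.** All of this is in the Statistical analysis section of the protocol article.

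- **Selection:** "Least absolute shrinkage and selection operator (LASSO) regression with tenfold cross-validation will be used for initial variable selection".
- **Tuning rule:** "This will select the subgroup of variables minimizing cross-validation error". No one-standard-error rule or other parsimony rule is stated.
- **Criterion:** "We will use the *C* statistic as the error measure to be optimized in the cross-validation process". The software named is glmnet.
- **Final estimator:** "Variables selected in the LASSO procedure will be used in an unpenalized multivariable logistic regression model".
- **Clinician input:** "Physician feedback regarding model complexity and variables necessary for inclusion will also be incorporated into the identification of the final prognostic model".

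The next paragraph of the section confirms which model is judged: "Performance of the unpenalized logistic regression model, fit using variables selected in the cross-validation procedure", together with any variables that clinicians consider necessary. Predicted probabilities come from that fitted model. It is applied to the external cohorts without recalibration, and recalibrated versions are optional.

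**The concern.** Cross-validation of a LASSO path scores the shrunken fits. A light penalty suits those fits because it limits shrinkage bias, and the price is a number of uninformative variables with very small coefficients. The refit removes the shrinkage and gives the same variables full-size coefficients, so the best penalty for the refit is usually heavier. The subset is thus optimal, at best, for a model that is not used.

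Two features make this hard to see from inside the derivation cohort. The C statistic depends only on ranks and cannot penalize predictions that are too extreme. Calibration of an unpenalized logistic fit in its own data is perfect by construction on intercept and slope.

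At stake are surplus predictors, each needing a validated definition, a live feed and a missing-value rule, and risks that are somewhat too extreme in new patients. The model is meant to give individual probabilities early in the stay and is to be deployed in a randomized trial, so calibration at high risk matters.

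**Working it through.** **No figure to reproduce.** The article states no event count, number of candidates, expected model size or expected calibration. The check therefore has a logical part and a simulation under stated assumptions.

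**Logical part.** The maximum-likelihood equations of the refit are Σ xⱼ(y − p̂) = 0 for the intercept and each variable j. Weighting them by the fitted coefficients and summing gives Σ LP(y − p̂) = 0, where LP is the linear predictor. Regressing y on LP in the same data then returns intercept 0 and slope 1, whatever the number of noise variables. Overfitting in calibration can first show in the external cohorts.

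**Simulation inputs.**
- From the article: "A retrospective cohort of 132,561 inpatient encounters (89,586 individual patients) at a large academic medical center will be collected".
- Assumed event rates 0.5%, 1.5% and 3%: 132,561 × 0.005 = 663, × 0.015 = 1,988, × 0.03 = 3,977 expected events.
- Assumed 80 or 150 candidates, of which 20 or 60 have a true effect; half binary, half continuous, correlated; C about 0.79.
- Planned rule: LASSO path, tenfold cross-validation maximizing the C of the penalized fit, then an unpenalized refit.
- Comparator: the same path and the same criterion (C), but scored on the unpenalized refit within folds (one-step approximation).
- Evaluation on 300,000 new records against true risk; 4 or 5 runs per setting. E/O is expected over observed in the top risk decile, relative to the overall ratio.

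Each cell shows planned rule / tuned on refit.

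| Rate, candidates, true | Mean events | Variables kept | Ratio | True predictors kept | Slope | E/O top decile | C |
|---|---|---|---|---|---|---|---|
| 3%, 80, 20 | 4,043 | 41.5 / 18.8 | 2.2 | 19.5 / 17.0 | 0.987 / 0.994 | 1.010 / 1.004 | 0.7915 / 0.7928 |
| 1.5%, 80, 20 | 2,007 | 44.6 / 31.8 | 1.4 | 19.2 / 16.8 | 0.966 / 0.974 | 1.033 / 1.025 | 0.7930 / 0.7924 |
| 1.5%, 150, 20 | 1,997 | 51.2 / 15.2 | 3.4 | 19.0 / 15.2 | 0.946 / 0.985 | 1.052 / 1.013 | 0.7873 / 0.7913 |
| 0.5%, 80, 20 | 680 | 35.2 / 19.0 | 1.9 | 16.4 / 14.4 | 0.928 / 0.951 | 1.075 / 1.049 | 0.7891 / 0.7937 |
| 0.5%, 150, 20 | 672 | 40.8 / 16.2 | 2.5 | 16.8 / 13.0 | 0.892 / 0.961 | 1.119 / 1.041 | 0.7846 / 0.7855 |
| 1.5%, 80, 60 | 2,022 | 71.2 / 56.8 | 1.25 | 57.0 / 50.5 | 0.966 / 0.968 | 1.032 / 1.030 | 0.7970 / 0.7923 |

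**Reading the table.**
- Slope differences with sparse signal: 0.007, 0.008 and 0.039 with about 2,000 events or more; 0.023 and 0.069 with about 670. With dense signal (last row): 0.002.
- Over-prediction in the top decile due to the mismatch alone: 0.2 to 3.9 points with about 2,000 events or more, 2.6 to 7.8 points with about 670.
- Ordinary overfitting remains. In the 1.5%, 80, 20 row the slope falls short of 1 by 0.034, of which 0.008 is the mismatch and 0.026 stays. In the dense row only 0.002 of 0.034 is the mismatch.
- The C difference runs from −0.0047 to +0.0046, with no consistent sign.
- Single runs vary. In one of the five runs at 1.5%, 80, 20, tuning on the refit kept more variables (73 against 61).

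**Second simulation.** With the same cohort size, 100 candidates and 3 runs per setting, sparse signal gave about 39 variables against 15 to 19. Slopes rose from 0.976 to 0.995 at 1.5% events and from 0.911 to about 0.954 at 0.6%, while C moved by −0.001 and +0.004. With nearly all candidates informative, the slope went from 0.958 to 0.959–0.961 at 1.5% and stayed at 0.899 at 0.6%. Held-out log-likelihood was never materially worse under tuning on the refit.

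**The case against.** The strongest counter-case starts from the Potential predictors section. Candidates were chosen for previously shown association with HA-VTE, so the dense setting may be the realistic one, and there calibration hardly moves. This stands as a limit on size.

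Tuning on the refit also discards signal: it lost 2 to 4 of the 20 true predictors in the sparse settings and 6.5 of 60 in the dense one. This stands and belongs in the stated downside.

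The plan has safeguards. LASSO is only the initial step, clinicians review complexity, and intercept, slope, integrated calibration index and curves are planned in three external cohorts, with recalibration allowed. These would reveal or soften a problem. They do not repair the tuning step: clinician review follows selection and has no stated out-of-sample criterion, and recalibrating the slope does not remove noise variables.

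Finally, this is a condensed article, and tuning detail is often left to an analysis plan. Here, however, the article itself fixes the rule, criterion, software and final estimator, and it is these that do not match.

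Three stronger readings are tempting and not supported:
- That the plan admits about twice as many variables as needed. The ratio to the comparator ran from 1.25 to 3.4, the ratio to the number of true predictors from 1.2 to 2.6, and the article gives none of the quantities that decide it.
- That the score will over-predict materially at high risk because of this step. With about 2,000 events or more, the step's share is small.
- That a slope below 1 will be misread as poor transportability. The article does not say so, and the temporal cohort from the same hospital helps to separate overfitting from change of place or population.

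**Conclusion.** The point holds as a mismatch between the model tuned and the model used. The claimed minimum of cross-validation error does not belong to the unpenalized refit, and nothing else in the article corrects this. Confidence is high for the mechanism and for its average direction, and not for its size.

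The size depends on assumed event rates, candidate numbers and sparsity. With many weak candidates, expect a visibly larger model and a slope lower by about 0.01 to 0.05, reaching 0.07 in the most extreme setting tried (672 events, 150 candidates). With mostly informative candidates, the model is about a quarter larger and the effect on calibration is close to nil. The simulations had few runs, no splines and no repeat encounters within patients.

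This is a worthwhile, inexpensive improvement and not a flaw that invalidates the model.

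**What to change.** In the Statistical analysis section, state that the penalty is chosen by the cross-validated error of the unpenalized refit: within each fold, select by LASSO at each penalty value, refit without penalty, and score the held-out fold. glmnet's relaxed fit with no shrinkage does this. Prefer binomial deviance as the criterion, since it responds to predictions that are too extreme, and continue to report C.

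Enter variables that clinicians already know they require with zero penalty before selection, so that the cross-validated model is the model used. If the team already intends to tune on the refit, one sentence saying so settles the point. At minimum, reword the claim that the subset minimizes cross-validation error.

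Cost: a change of arguments in the same R package and one or two sentences, with no new data. Downside: the model will usually be smaller and may omit some weak true predictors, with negligible change in C. Some overfitting will remain, so a slope slightly below 1 in the external cohorts should still be expected.

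### Derivation-cohort results are apparent performance: calibration intercept and slope are fixed at 0 and 1 by the fitting method, and C is modestly optimistic

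*Protocol article*

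**What the plan says.** The relevant text is in the Protocol article, Statistical analysis.

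- Data for development: "Model development will be performed within the derivation cohort described above". The abstract gives its size as 132,561 encounters in 89,586 patients.
- Role of cross-validation: LASSO "regression with tenfold cross-validation will be used for initial variable selection", and "We will use the *C* statistic as the error measure to be optimized in the cross-validation process".
- Final estimator: "Variables selected in the LASSO procedure will be used in an unpenalized multivariable logistic regression model". Variables that clinicians consider necessary are added.
- Where performance is shown: results for the refitted model "will be reported in the derivation cohort as well as the temporal, domain, and geographic external validation cohorts".
- Source of the predictions: "Predicted probabilities for each patient will be generated using the fitted logistic regression model object", using R's predict function.
- External cohorts: they play no part in development and are scored first with the model as fitted. If performance falls substantially, recalibrated coefficients may be considered. "In such cases, recalibrated and non-recalibrated model performance will be reported and compared".

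The article does not call the derivation figures apparent and mentions no optimism correction. It does not name the reference against which a fall is judged, the type of recalibration, or the data on which a recalibrated model is assessed.

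**The concern.** Cross-validation serves only to choose variables. The model that is reported has no shrinkage, and its predictions in the derivation cohort come from the fit to those same encounters. A reader who sees a derivation slope of 1.00 and intercept of 0.00 may take them as evidence of good calibration, when any unpenalized logistic model would show them. The derivation C was maximised twice on the same data, once in selection and once in fitting.

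Two uses are at stake. One is the derivation column of the results itself. The other is the decision to recalibrate: if the apparent figures are the reference, part of any drop in an external cohort is ordinary overfitting rather than a difference in period, place or population. A similar question arises if a recalibrated model is scored in the cohort that recalibrated it.

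**Working it through.** The article states no C statistic, calibration figure, event rate or parameter count, so there is no figure of its own to reproduce.

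**1. Intercept and slope in the fitting data.** Let p_i be the fitted risk and LP_i = b0 + Σ_j b_j x_ij. Maximum likelihood solves Σ(y_i − p_i) = 0 and Σ x_ij(y_i − p_i) = 0 for every j. The calibration model logit P(y=1) = a + s·LP has score equations Σ(y_i − q_i) = 0 and Σ LP_i(y_i − q_i) = 0. At a = 0 and s = 1, q_i = p_i. The first equation is then the intercept equation of the fit, and the second is the sum of the fitted equations weighted by b0 and the b_j. Both are zero and the likelihood is concave, so (0, 1) is the solution for any data and any set of variables.

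**2. The other calibration measures.** These are not forced. In one run with an omitted quadratic term, intercept and slope were still exactly 0 and 1, while ICI was 0.00766 at an event rate of 0.02294: 0.00766 / 0.02294 = 0.33, a third of the event rate.

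**3. Size of the optimism.** Inputs:

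- n = 132,561 (abstract).
- Event rate 0.5–2%, assumed: 0.005 × 132,561 ≈ 663 to 0.02 × 132,561 ≈ 2,651 events.
- 40 or 100 fitted parameters, assumed; 20 have a true effect and true C is about 0.81.
- Independent normal predictors, 20 replicates per setting, each model scored in its own data and in a new sample from the same population.

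| Parameters | Event rate | C, own data | C, new data | Difference (SE) | Slope, own data | Slope, new data |
|---|---|---|---|---|---|---|
| 40 | 0.5% | 0.8159 | 0.8069 | 0.0090 (0.0027) | 1.000 | 0.962 |
| 40 | 1% | 0.8125 | 0.8055 | 0.0070 (0.0022) | 1.000 | 0.973 |
| 40 | 2% | 0.8079 | 0.8048 | 0.0031 (0.0012) | 1.000 | 0.986 |
| 100 | 0.5% | 0.8216 | 0.7972 | 0.0244 (0.0026) | 1.000 | 0.898 |
| 100 | 1% | 0.8144 | 0.8045 | 0.0099 (0.0016) | 1.000 | 0.953 |
| 100 | 2% | 0.8081 | 0.8023 | 0.0058 (0.0013) | 1.000 | 0.975 |

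ICI was lower in the model's own data in all six settings (0.00045–0.00111 against 0.00066–0.00126), a gap of 0.00015–0.00031. Brier score was not computed.

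A harsher setting used 15 true predictors, 60 or 120 terms all kept, and only two replicates. It gave C differences of 0.012 (0.733 − 0.721), 0.019 (0.733 − 0.714) and 0.031 (0.743 − 0.712), with new-data slopes of 0.94, 0.89 and 0.85. It is a high-end case and is not relied on here.

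Neither simulation ran the LASSO step. The 20-replicate simulation also left out repeat encounters (132,561 / 89,586 = 1.48 per patient).

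**4. Recalibration scored in the same cohort.** An external cohort of an assumed 60,000 with shifted intercept and slope was used.

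- Intercept-plus-slope recalibration gave intercept 0 and slope 1 exactly, by the algebra in step 1. C did not change (for example 0.7598 before and after), because a positive linear change of LP keeps the ranking.
- Re-estimating every coefficient also gave 0 and 1, and C was inflated by 0.006–0.035 (40 parameters) or 0.017–0.057 (100 parameters). These differences are noisy: the same comparison for the intercept-plus-slope model, where C has no recalibration optimism, ranged from −0.006 to 0.010.

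**The case against.** The strongest reply is that the evidence that matters is external. Three cohorts are kept out of development and scored first with the model as fitted, so any over-extreme predictions would show in their calibration slopes. Nowhere is derivation performance presented as validation. This stands, and it limits the weight of the point.

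A second reply is that a condensed article may leave internal resampling to a fuller plan. That would answer a mere silence. Here, however, the article names the estimator, the cohort and the prediction function, and following those steps gives uncorrected figures.

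A third reply is that the optimism is small at this sample size. In five of the six settings C moved by 0.010 or less and the new-data slope was 0.95 or higher. This stands as to size, subject to the assumptions.

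Four stronger readings are tempting, and the document does not support them:

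- *All derivation calibration is perfect by construction.* Only intercept and slope are. ICI, Brier score and the calibration curve can show misfit.
- *Overfitting will be mistaken for a population difference.* The article does not say that apparent performance is the reference for a drop, and gaps of the size found need not trigger anything.
- *A recalibrated model must win.* Same-cohort scoring is only inferred from the absence of a stated split. Even then, intercept-plus-slope recalibration cannot improve C, and the non-recalibrated results are reported alongside.
- *The external results are compromised.* The non-recalibrated ones carry no fitting optimism.

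**Conclusion.** The point holds in a limited form. The derivation intercept and slope will be 0 and 1 whatever the quality of the model; this is algebra and needs no assumption. The derivation C will be optimistic, by about 0.003–0.024 with new-data slopes of 0.90–0.99. That range rests on the assumed event rates and parameter counts, a true C near 0.81, independent predictors, and no selection step or within-patient clustering. Either omission could move it. The consequence for decisions is conditional: apparent figures are a biased yardstick only if they are the yardstick. The recalibration part is likewise conditional on scoring in the same cohort, and extends to C only if individual coefficients are re-estimated. The change is worth making because it is cheap and makes the derivation figures informative.

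**What to change.** 1. Label derivation-cohort performance as apparent.
2. Add optimism-corrected C, calibration slope and ICI from a bootstrap that resamples patients with all their encounters. In each resample, repeat the median imputation, the LASSO with tenfold cross-validation and the unpenalized refit, holding the clinician-required variables fixed.
3. State that these corrected figures are the reference for any drop in an external cohort.
4. Name the type of recalibration (intercept, intercept and slope, or all coefficients). Assess a recalibrated model by cross-validation within the validation cohort or on a part of it not used to recalibrate.

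The cost is computing time, a paragraph of text, and slightly less favourable derivation figures. Multiplying the linear predictor by the bootstrap slope before external validation is an option, not part of the required change. The bootstrap does not undo the fact that the earlier model described in the Background was developed at the same hospital over the same dates; that does not affect the external cohorts.
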